**Figure 2 figure2:**
[figure not shown]
Flowchart of assessments before, during, and after 10 intervention sessions. BSQ: Body Shape Questionnaire; CAM: cardiovascular autonomic modulation; DASS-21: Depression, Anxiety, and Stress Scale; DXA: dual-energy x-ray absorptiometry; FR24h: 24-hour food recall; HADS: Hospital Anxiety and Depression Scale; HDL: high-density lipoprotein; HIIT: high-intensity interval training; HRMAX: maximum heart rate; IPAQ: International Physical Activity Questionnaire (characterization); LDL: low-density lipoprotein; NC: neck circumference; PSQI: Pittsburgh Sleep Quality Index; TUS: therapeutic ultrasound; usCRP: ultrasensitive C-reactive protein; WC: waist circumference; WHR: waist-to-hip ratio.

### Group 3: HG

Participants in the HG receive the same treatment as those the AG. However, after the application of TUS plus Aussie current, they will not perform HIIT.

### Outcomes

#### Primary Outcomes

The primary outcomes involve a comparison (between groups) of the effect of 10 sessions of combined therapy (TUS+Aussie current) alone versus in combination with HIIT, specifically on abdominal SAT thickness, body composition, metabolic profile, and serum glycerol release.

#### Secondary Outcomes

Secondary outcomes assess the impact on CAM, sleep quality, anxiety, depression, body image concerns, and blood biochemical variables (Table 2).

**Table 2 table2:** Primary and secondary outcomes of the study.

Variable		Description
**Primary outcomes**		
	Abdominal subcutaneous adipose tissue (cm)	Ultrasound imaging [4,24]
	Body composition (kg; percentage and grams)	Dual-energy x-ray absorptiometry [30]
	Metabolic profile	Venous blood collection Hydrogen nuclear magnetic resonance [34,66]
**Secondary outcomes**		
	Cardiovascular autonomic modulation	Heart rate and arterial pressure variability [36,38,40,41]
	Sleep quality (score)	Pittsburgh Sleep Quality Index [46,47]
	Anxiety, depression, and stress (score)	Hospital Anxiety and Depression Scale [67] Depression, Anxiety, and Stress Scale [48]
	Body image (score)	Body Shape Questionnaire [49]
	Blood tests	Complete blood count, glycated hemoglobin, fasting glucose, ultrasensitive C-reactive protein, total cholesterol, high-density lipoprotein, low-density lipoprotein, and triglycerides
	Perimetry measurements (cm)	Waist-to-hip ratio, waist-to-height ratio, neck circumference, and waist circumference

### Monitoring Adverse Events

There is a possibility that participants may experience side effects in response to the study protocol. Regarding HIIT, intense shortness of breath, generalized tiredness, and dizziness may occur, and this will be recorded in the study. In addition, as the study involves blood sampling, there is a possibility of damage not directly related to the intervention. The expected adverse effects, such as bruising and local pain, will be monitored. Any adverse effects other than these will be recorded and reported, although such occurrences are considered highly unlikely. During assessments and sessions, participants will also be asked about their well-being and whether they have experienced any changes or symptoms since the start of the study. This information will be documented to ensure the ongoing safety and monitoring of the participants.

Participant safety will be prioritized throughout the study. Initially, general health status will be assessed, including a treadmill stress test supervised by a cardiologist to detect cardiovascular contraindications to high-intensity exercise.

A total of 30 days before starting the intervention (TUS+Aussie current), all participants (all 3 groups) will receive identical printed guidelines containing joint mobility and stretching exercises (ankle, hip, and spine) to be performed 2 to 3 times a week. The aim will be to reduce the problems caused by a sedentary lifestyle in the joints and, thus, reduce the risk of injury during HIIT. As a way of monitoring adherence, all participants will complete a weekly form on how often they stretch.

During the HIIT sessions, HR will be monitored continuously, and perceived exertion will be assessed using the Borg scale. Immediate interruption of the session will be planned if signs of intolerance occur (eg, dizziness, chest pain, and syncope). During the application of TUS+Aussie current, participants’ comfort will be monitored using a paresthesia perception scale from 0 to 10, aiming for a level of sensation of approximately 5, with adjustments made whenever necessary. All interventions will strictly follow the safety criteria and contraindications recommended by the equipment manufacturer. In case of adverse events, participants will be clinically assessed and, if necessary, withdrawn from the study to ensure their safety.

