#### Session Scheduling and Follow-Up

To minimize data loss, participants receive reminders about the date and time of each session. Physiotherapists responsible for interventions may also call participants if necessary to confirm appointments. For evaluations and re-evaluations, the blinded evaluator contacts the participants via telephone. At the end of the 10 treatment sessions, the re-evaluation is scheduled between 3 and 15 days after the last session.

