### Statistical Analysis

#### Sample Size

The primary outcome, percentage of body fat, was used to calculate the required sample size using the RStudio software (version 12.1; Posit PBC) assuming a moderate expected effect size of *ƒ*≥0.15 and a significance level of 5% and to promote a statistical power of 80%. A total of 18 participants per group is necessary to achieve 80% statistical power with an α level of 5%. Considering a dropout of 10%, the target sample size was increased to 20 participants per group, with the total sample size being 60 individuals. Appropriate statistical corrections (eg, Bonferroni or false discovery rate) will be applied to the *P* values, recognizing the necessity of conducting multiple tests due to the analysis of additional results.

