#### Statistical Methods for Primary and Secondary Outcomes

Data analysis will be conducted by a researcher blinded to the participants’ allocation to the groups. The data will be entered into a Microsoft Excel spreadsheet for subsequent analysis.

For quantitative variables, the assumption of normality of data distribution and homogeneity of variances will be checked using the Shapiro-Wilk test and Levene test, respectively. To compare participant characteristics at baseline between groups, a 1-way ANOVA or Kruskal-Wallis test will be applied when appropriate. For comparisons between groups involving categorical variables, the chi-square test or Fisher exact test will be used. To compare primary and secondary outcomes between and within groups, linear mixed models estimated using the maximum likelihood method with an appropriate covariance matrix structure will be used assuming group (AG, PG, and HG), moment (before and after the intervention) or time (baseline, after TUS+Aussie current, and after HIIT), and interactions (group-moment, group-time, moment-time, and group-moment-time) as fixed factors and participants as a random factor [66]. In addition, moment and time will be assumed as a repeated-measure effect. The model that fits the data will be the one with the minimum Akaike information criterion. When appropriate, the data may be subjected to a Box-Cox transformation to better adhere to a normal distribution [69,70]. Whenever a significant *F* value is obtained in the ANOVA or linear mixed models, a Sidak post hoc adjustment for the purpose of pairwise multiple comparisons will be applied. The significance level will be set at 5% (*P*<.05). All analyses will be conducted using the PASW Statistics software (version 25.0; SPSS).

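### Read as written, the adverse-event withdrawal rule ends outcome collection as well as treatment, and any such losses would fall more on the two HIIT arms than on HG

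*Protocol article*

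**What the plan says.** All references are to the protocol article.

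- **Monitoring Adverse Events** sets the rule: "In case of adverse events, participants will be clinically assessed and, if necessary, withdrawn from the study to ensure their safety". The same section provides for interrupting a HIIT session if signs of intolerance appear. It describes nothing between that and leaving the study.
- The same section names the expected effects of exercise: "Regarding HIIT, intense shortness of breath, generalized tiredness, and dizziness may occur, and this will be recorded in the study". The other expected effects it lists, bruising and local pain, relate to blood sampling.
- **Group 3: HG** separates the arms on this exposure: "However, after the application of TUS plus Aussie current, they will not perform HIIT". AG and PG follow the same HIIT protocol.
- **Session Scheduling and Follow-Up** times the final assessment by completed treatment: "At the end of the 10 treatment sessions, the re-evaluation is scheduled between 3 and 15 days after the last session". It gives no timing for participants who stop early.
- **Table 1** places SAT and body composition at weeks −4, 0 and 6, so only week 6 falls after the intervention has started.
- **Primary Outcomes** names the contrast of interest as the "effect of 10 sessions of combined therapy (TUS+Aussie current) alone versus in combination with HIIT".
- **Statistical Methods for Primary and Secondary Outcomes** specifies that "linear mixed models estimated using the maximum likelihood method with an appropriate covariance matrix structure will be used".
- **Sample Size** allows for 10% dropout, the same in every group.

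**The concern.** Stopping an intervention and leaving a trial are different events, and the adverse-event text provides only for the second. Because the re-evaluation is tied to the tenth session, nothing in the article brings a participant who stopped early back for the week 6 ultrasound and DXA.

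The losses would probably not be balanced. The exertional effects, the session-interruption provision and the remarks on injury risk all concern HIIT, so withdrawals under this rule are more likely in AG and PG than in HG. If those withdrawn would also have responded differently, the comparison of combined therapy with and without HIIT shifts towards people who tolerated HIIT. That fits poorly with a trial that calls itself pragmatic and aims to tell practitioners whether the combination works better than one therapy alone. An analysis plan cannot recover measurements that were never taken.

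**Working it through.** **1. The plan's only attrition figure.** Sample Size needs 18 evaluable per group and allows 10% dropout: 18 / (1 − 0.10) = 20 per group, 60 in total. This reproduces.

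**2. What that allowance covers.** It protects precision, not balance. Suppose 15% are lost in each HIIT arm and none in HG:
- AG: 20 × 0.85 = 17
- PG: 20 × 0.85 = 17
- HG: 20
- Total: 17 + 17 + 20 = 54 = 3 × 18

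The planned evaluable total is met although the loss is entirely one-sided. The 15% is hypothetical.

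**3. Bias formula.** Let *p* be the share of an arm withdrawn before week 6. Let *d* be the amount, in SD of change, by which those withdrawn would have changed less than those retained. The mean change over everyone randomised is (retained mean) − *p* × *d*, so using retained participants overstates the arm's change by

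bias = *p* × *d*.

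For SAT and DXA a withdrawn participant contributes only pre-intervention values. The mixed model can adjust for differences in those values but has no post-treatment value for that person. So *d* should be read as the difference that remains once the pre-intervention values are accounted for. If data are missing at random given the observed data, *d* = 0 and the bias is 0.

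**4. Illustration.** The article gives no adverse-event or withdrawal rate. Assumptions: 1 or 2 of 20 withdrawn in one HIIT arm, none in HG, *d* = 0.5 or 1.

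| Withdrawn in HIIT arm | *p* | *d* = 0.5 SD | *d* = 1 SD |
|---|---|---|---|
| 1 of 20 | 0.05 | 0.025 SD | 0.05 SD |
| 2 of 20 | 0.10 | 0.05 SD | 0.10 SD |

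Under these assumptions the contrast with HG is tilted in favour of HIIT by 0.025 to 0.10 SD. If HG loses similar participants at the same rate, the bias cancels. It largely cancels in AG versus PG, where both arms perform HIIT.

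**5. With outcomes still collected.** If those who stop early attend week 6, *p* from this rule is 0 for the week 6 outcomes, and so is the bias it causes.

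**The case against.** The strongest reply is that the article never says assessments stop. It says withdrawal follows only if necessary, and whether withdrawn participants are followed up is something an article may leave to the full protocol. Study Assessments and Timeline also says that all participants attend a final visit at week 6. In part this stands: the loss of week 6 data is an inference from the withdrawal sentence together with the scheduling sentence. But both sentences are stated rules, not silence. A person withdrawn from the study is no longer plainly covered by a statement about participants, so the passages need reconciling.

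Second, withdrawals may be few. Participants are healthy adults aged 18 to 40, screened by ECG and a supervised stress test, and the listed symptoms are to be recorded, not treated as grounds for withdrawal. HG also receives active therapy, so zero loss there is an assumption. This stands and limits the likely size.

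Third, maximum likelihood keeps the pre-intervention data and is valid under missing at random. This also stands. A reader might infer that the model reduces to an analysis of those who tolerated treatment, but that would require missingness that depends on unobserved response, which is possible but not shown.

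A reader might also express the bias as a share of the effect implied by *f* = 0.15. The documents do not support that. Read as a one-way between-group effect, *f* = 0.15 with 54 evaluable gives power of about 0.15, not the stated 80%, so the scale of *f* is not established. Nor can the whole 10% allowance be assigned to adverse events in HIIT arms, since it is not specific to cause or arm.

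**Conclusion.** The point holds in a limited form. The wording, followed literally, ends outcome collection together with the intervention. Any resulting losses would plausibly be more frequent in AG and PG than in HG. The comparison at risk is combined therapy alone versus combined therapy with HIIT, for outcomes with one post-intervention measurement (SAT and DXA).

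The size is unknown. The 0.025 to 0.10 SD range rests on assumed counts (1 to 2 of 20, none in HG) and an assumed 0.5 to 1 SD smaller change, neither of which comes from the documents. The bias is zero under missing at random. The documents do not support saying that the trial expressly discards these outcomes, that such withdrawals will be common, or that the placebo-controlled contrast is compromised. The case for acting is that the remedy is cheap and unmeasured outcomes cannot be recovered later.

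**What to change.** - **Monitoring Adverse Events:** reword so that stopping the intervention and leaving the study are separate. The clinical decision on who stops the intervention stays exactly as it is.
- **Session Scheduling and Follow-Up:** state that participants who stop early are still invited to the week 6 assessment (SAT, DXA, perimetry, questionnaires and biochemistry), unless they withdraw consent or the assessment is clinically unsuitable for them.
- **Statistical Methods:** state that they are analysed in the arm to which they were randomised.

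**Limit.** The metabolic and glycerol samples are drawn around a treatment session (Serum Metabolic Profile), so they are outside this fix.

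**Cost.** The week 6 visit is already scheduled. The change means a small protocol amendment while the trial is under way, with consent material checked for consistency, and a few off-treatment assessments, which may slightly dilute the estimated effect.

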### Statistical Analysis

#### Sample Size

The primary outcome, percentage of body fat, was used to calculate the required sample size using the RStudio software (version 12.1; Posit PBC) assuming a moderate expected effect size of *ƒ*≥0.15 and a significance level of 5% and to promote a statistical power of 80%. A total of 18 participants per group is necessary to achieve 80% statistical power with an α level of 5%. Considering a dropout of 10%, the target sample size was increased to 20 participants per group, with the total sample size being 60 individuals. Appropriate statistical corrections (eg, Bonferroni or false discovery rate) will be applied to the *P* values, recognizing the necessity of conducting multiple tests due to the analysis of additional results.

#### Descriptive Statistics and Baseline Data

A CONSORT (Consolidated Standards of Reporting Trials)-style flowchart [68] will present the number of patients selected and all reasons for exclusion before randomization. Demographic and socioeconomic information, including age, sex, race, socioeconomic status, and educational level, as well as baseline clinical characteristics such as BMI, glycated hemoglobin, smoking status, alcohol consumption, and comorbidities, among other variables, will be described by study arm and overall. Categorical variables will be reported as absolute numbers and percentages. Continuous variables with a reasonably symmetrical distribution will be summarized as means and SDs. For highly skewed continuous variables, medians and IQRs will be used.

#### Statistical Methods for Primary and Secondary Outcomes

Data analysis will be conducted by a researcher blinded to the participants’ allocation to the groups. The data will be entered into a Microsoft Excel spreadsheet for subsequent analysis.

For quantitative variables, the assumption of normality of data distribution and homogeneity of variances will be checked using the Shapiro-Wilk test and Levene test, respectively. To compare participant characteristics at baseline between groups, a 1-way ANOVA or Kruskal-Wallis test will be applied when appropriate. For comparisons between groups involving categorical variables, the chi-square test or Fisher exact test will be used. To compare primary and secondary outcomes between and within groups, linear mixed models estimated using the maximum likelihood method with an appropriate covariance matrix structure will be used assuming group (AG, PG, and HG), moment (before and after the intervention) or time (baseline, after TUS+Aussie current, and after HIIT), and interactions (group-moment, group-time, moment-time, and group-moment-time) as fixed factors and participants as a random factor [66]. In addition, moment and time will be assumed as a repeated-measure effect. The model that fits the data will be the one with the minimum Akaike information criterion. When appropriate, the data may be subjected to a Box-Cox transformation to better adhere to a normal distribution [69,70]. Whenever a significant *F* value is obtained in the ANOVA or linear mixed models, a Sidak post hoc adjustment for the purpose of pairwise multiple comparisons will be applied. The significance level will be set at 5% (*P*<.05). All analyses will be conducted using the PASW Statistics software (version 25.0; SPSS).

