### Randomization and Blinding

In this study, the researchers responsible for the evaluations and those analyzing the data will be blinded. To ensure the feasibility of blinding, the blinded research teams will not participate in the interventions, and all information will be coded to prevent the identification of participants and intervention groups. The effectiveness of blinding will be assessed using a questionnaire completed by the evaluators at the end of the final assessment for each data collection block.

After the initial assessments, participants will be stratified (age range, sex, and fat mass index) and randomly assigned to 1 of 3 groups. Participants in group 1 (active TUS+Aussie current with HIIT [AG]) will undergo combined therapy (TUS+Aussie current) along with the HIIT protocol. Participants in group 2 (placebo for TUS+Aussie current with HIIT [PG]) will undergo placebo combined therapy (TUS+Aussie current) with the devices turned off along with the HIIT protocol. Participants in group 3 (TUS+Aussie current–only group [HG]) will receive only the combined therapy (TUS+Aussie current) without the HIIT protocol.

For stratified randomization, participants will be initially grouped into blocks based on similar characteristics, including age range (20-29 years or 30-40 years), sex (male or female), and fat mass index (overweight, grade-I obesity, or grade-II obesity). These characteristics will be chosen to control for potential confounding factors. Within each block, participants will be then randomized into the 3 study groups using Microsoft Excel, ensuring an unbiased allocation process. Block sizes were not fixed, further reducing the risk of allocation predictability. The randomization process will be conducted by a researcher designated exclusively for this task, who will have no contact with the study participants or the researchers involved in data collection. This researcher will also be responsible for generating random alphanumeric codes to ensure the anonymity of each participant’s information.

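### The stated mixed model omits the stratification factors, uses a change-score contrast where baseline adjustment would be more precise, and fixes maximum likelihood at 54 to 60 participants

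*Protocol article*

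**What the plan says.** All references are to the protocol article.

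- **Randomization and Blinding:** "participants will be stratified (age range, sex, and fat mass index) and randomly assigned to 1 of 3 groups". The levels are two age ranges, two sexes and three fat mass index classes. The stated reason is: "These characteristics will be chosen to control for potential confounding factors".
- **Statistical Methods for Primary and Secondary Outcomes, estimator and first fixed factor:** "linear mixed models estimated using the maximum likelihood method with an appropriate covariance matrix structure will be used assuming group (AG, PG, and HG"). No method for the degrees of freedom is named.
- **Same section, how baseline enters:** the model contains "moment (before and after the intervention) or time (baseline, after TUS+Aussie current, and after HIIT"). The pre-intervention value is therefore one level of the outcome.
- **Same section, remaining terms:** "interactions (group-moment, group-time, moment-time, and group-moment-time) as fixed factors and participants as a random factor". No stratification factor and no baseline covariate is listed.
- **Sample Size:** 18 evaluable participants per group, raised to 20 per group for 10% dropout.

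**The concern.** The design controls three characteristics at randomisation, and the stated model then uses none of them. Baseline values are collected for the before/after outcomes, but each group keeps its own free baseline mean. The group-by-moment test therefore compares changes and does not use how strongly the baseline value predicts the later one. Maximum likelihood estimates the variance without allowing for the fitted group means, which matters in a trial this small. At stake are precision that data already collected could supply, and an error rate that differs somewhat from the nominal 5%.

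**Working it through.** **Inputs.** Three arms at 1:1:1 (Study Design); 5% significance level (Statistical Methods); 18 or 20 per group (Sample Size). The dropout step reproduces: 18/0.9 = 20. So N = 54 evaluable or 60 randomised. The before/after correlation ρ and the share of change variance explained by the strata (R²) are not given, so the values below are assumptions. Data are taken as complete at two moments.

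**1. What the model tests.** With complete two-moment data, the group-by-moment test is a one-way analysis of variance of the change scores.

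**2. Baseline.** For outcome variance σ² at each moment:
- change score: variance 2σ²(1−ρ)
- adjusted for baseline: variance σ²(1−ρ²)
- ratio, adjusted to change: (1+ρ)/2

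| assumed ρ | ratio | variance reduction | SE reduction |
|---|---|---|---|
| 0.5 | 0.75 | 25% | 13.4% |
| 0.75 | 0.875 | 12.5% | 6.5% |
| 0.9 | 0.95 | 5% | 2.5% |

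**3. Maximum likelihood alone.** The variance estimate is SSE/N instead of SSE/(N−3).
- N = 54: SE ratio √(51/54) = 0.972, so 2.8% too small.
- N = 60: SE ratio √(57/60) = 0.975, so 2.5% too small.

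The type I error is P(F with 2 and N−3 df > critical value × (N−3)/N). This gives about 5.9% at N = 54 and 5.8% at N = 60. Simulation of 200,000 null trials gives 5.9–6.0% and 5.7%. Dividing by N−3 returns 5.0% and 4.9%. A single pairwise t test before the Sidak step runs at about 5.7% (N = 54) or 5.6% (N = 60).

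**4. Omitted strata, keeping maximum likelihood.** Balanced strata that predict change inflate the residual variance without inflating the differences between groups, so the test becomes conservative. Simulated type I error (100,000 null trials):

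| assumed R² | N = 54 | N = 60 |
|---|---|---|
| 0% | 5.9% | 5.7% |
| 3% | 5.4% | 5.2% |
| 5% | 5.1% | 4.9% |
| 10% | 4.3% | 4.3% |

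An F approximation at N = 54 gives 5.2% at R² = 5% and 4.5% at 10%, which agrees.

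**5. How strata must enter.** In 200 fitted mixed models at N = 54, adding a stratum main effect left the group-by-moment estimate the same and the SE ratio at 1.000. Only stratum-by-moment terms, or strata as covariates in a model of the post-treatment value, can sharpen the contrast.

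**6. Adding terms without changing the estimator.** Four stratum-by-moment terms (1 for age range, 1 for sex, 2 for fat mass index class) leave 54 − 3 − 4 = 47 residual df. Maximum likelihood still divides by 54. The type I error becomes about 7.4%.

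**The case against.** Four stronger readings are tempting, and the article does not support them.

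- **That baseline is ignored.** It is not. Moment and group-by-moment are in the model, and a change-from-baseline contrast is unbiased under randomisation. Adjustment improves efficiency; it does not correct an error.
- **That the P values are too small.** This follows from maximum likelihood only, and by less than about 1 percentage point. Omitting strata that predict change pushes the other way, and at R² of 5–10% it offsets or outweighs the first effect.
- **That a large gain is being lost.** At ρ = 0.5 the gain would be like having 54/0.75 = 72 participants, but that is the most favourable value considered. Body fat percentage, the outcome used for sizing, is measured by DXA over a short interval in both sexes, from overweight to grade-II obesity. That wide spread between people makes a high ρ and a small gain more plausible. Questionnaire, autonomic and serum outcomes use the same model and may have a lower ρ.
- **That the covariance is over-specified,** because the model has "participants as a random factor" and also says: "In addition, moment and time will be assumed as a repeated-measure effect". No unstructured matrix is named, and the model is chosen by minimum Akaike criterion. With two occasions a redundant random intercept leaves the fitted covariance and the tests unchanged. The metabolic profile, with several samples at each of two sessions, can support both terms. No result is affected.

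Two further objections carry weight. The benefit from the strata has no documented size. The Discussion expects participants with more fat to benefit more in the active group, but that is a hypothesis. Covariates might also be set in an analysis plan that is not shown. The estimator and the list of factors, however, are stated in the article.

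**Conclusion.** The point stands as a modest, inexpensive improvement. The planned contrast is valid. Compared with baseline adjustment it gives up between 5% and 25% of variance over the assumed ρ of 0.9 to 0.5, probably near the lower end for DXA body fat. Maximum likelihood on its own moves a 5% test to about 5.7–5.9%. Once the omitted strata are counted, the net error may lie above or below 5%, and the article gives no figure that settles which. These sizes assume complete data, equal arms and balanced strata. The two distortions cannot be relied on to cancel.

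**What to change.** - **Outcomes measured before and after treatment:** model the post-treatment value on group, with the pre-intervention value, sex, age range and fat mass index class as covariates. An alternative is a repeated-measures model with a common baseline mean and stratum-by-moment terms. Name the pre-intervention value to be used: the text places baseline at week −1, while Table 1 marks weeks −4 and 0. The age ranges also start at 20 years although entry is from 18, so the covariate needs a definition that covers everyone.
- **Metabolic profile:** this is sampled in weeks 1 and 5 with several samples per session, so keep the repeated-measures model and give it a common pre-session mean at week 1.
- **All models:** fit by REML with Satterthwaite degrees of freedom.
- **Make these changes together.** Adding terms while keeping maximum likelihood would worsen the error rate (about 7.4% in the case above).

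The cost is analysis wording and about 5 degrees of freedom (1 for baseline, 1 for sex, 1 for age range, 2 for fat mass index class). All the covariates are already collected. The article places analysis after the last reassessment, so the wording can be settled before then.
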